### Participant timeline {13}

**Table Tabb:** 

Time point	Study period								Follow-up
	Prenatal postnatal allocation post-allocation discharge								
			0–4 h after delivery	0 h	48 h	72 h	168 h	> 28 days PNA	2, 5.5, 8 years
**Enrollment**									
Eligibility screen	X	X							
Informed consent	X	X		X	X				
Allocation			X						
**Standard care**									
Empiric antibiotics Blood culture Presepsin analysis		X	X	X	X	X	X		
**Intervention (presepsin-guided)**									
Empiric antibiotics				X	X	X	X		
No antibiotics				X	X	X	X		
Escape antibiotics Blood culture Presepsin analysis		X	X	X	X	X	X		
**Assessments**									
Blood sample*			X						
Sepsis-related severity of illness				X	X	X	X		
Culture-proven EOS				X	X	X			
Incidence of NEC, LOS, death								X	
Incidence BPD, ROP, IVH, PVL								X	
Demographics, clinical variables	X	X	X	X	X	X	X		
Neurodevelopmental outcome								X	X
Economic evaluation				X	X	X	X	X	X

SPIRIT figure. This participant timeline applies for patients in the RCT part of the study

*0.5 mL umbilical cord blood or during first regular blood draw

*BPD* bronchopulmonary dysplasia, *EOS* early-onset sepsis, *IVH* intraventricular haemorrhage, *LOS* late-onset sepsis, *NEC* necrotizing enterocolitis, *PNA* postnatal age, *PVL* periventricular leukomalacia, *ROP* retinopathy of prematurity

### Sample size {14}

Incidence of culture-proven EOS is assumed to be 1.4% based on the most recent and largest cohort with identical GA (< 32 weeks, *N* = 43,178) [4] and confirmed by screening 4 years admission data (2016–2019) of the NICU of Erasmus MC (Rotterdam, The Netherlands). With a plasma presepsin cutoff of 645 pg/ml, sensitivity is 100% (95% CI 78–100%) and specificity is 54% (95% CI 41–62%) for detecting EOS [14]. To balance the feasibility and the safety of the study, we have chosen a non-inferiority margin of 2% for the absolute between-RCT-arms difference in culture-proven EOS incidence (intervention–control) [24]. We deem this extra absolute risk acceptable in light of the incremental daily increased risk of adverse events with administration of antibiotics (NEC, LOS, death) [7]. Assuming there is no difference in culture-proven EOS between both study groups, a sample size of 427 is needed in both study groups (total *N* = 854), using a two-group, large-sample normal approximation test of proportions with 80% power and 1-sided 5% significance level. For the co-primary superiority outcome unnecessary antibiotics prescription < 72 h after birth, it is estimated that approximately 70% of all infants in the control group will discontinue antibiotics within 72 h (ref). Based on expert opinion, we consider an absolute reduction of 30% or more clinically relevant. Based on the aforementioned diagnostic accuracy of a presepsin cut-off level of 645 pg/ml, with a number of 427 in both study groups, we expect to detect a 30% reduction in the co-primary superiority outcome with a power of 99% and a 2-sided alpha of 0.05 (two-group Fisher’s-exact test). To allow for some unassessable cases (e.g. based on technical issues or withdrawn consent, estimated at 5%), a number of 450 will be included in both RCT-arms. The total study population is estimated to consist of 20% low risk (*N* = 244), 70% moderate risk (*N* = 900), and 10% high risk infants (*n* = 122).

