### Trial design {8}

This is a multicentre, parallel groups, superiority and non-inferiority RCT with a concurrent observational study and is visualized in Fig. 1. The allocation ratio of the RCT is 1:1 in the intervention and comparator arm.

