## Statistical methods

### Statistical methods for primary and secondary outcomes {20a}

Analyses for both co-primary outcomes will be performed using the intention-to-treat principle and additionally using the per-protocol principle for the co-primary non-inferiority outcome to evaluate consistency of both analysis approaches compliant with recommendations for non-inferiority analyses [25]. The absolute between-RCT-groups difference in the co-primary non-inferiority outcome (incidence of culture-proven EOS) (intervention—control) with its one-sided 95% confidence interval (CI) will be calculated. When the upper limit of this one-sided 95% CI is below 2%, non-inferiority can be claimed. The between-RCT-groups difference in proportions of the co-primary superiority outcome (unnecessary antibiotics administration) will be studied under a common superiority hypothesis and expressed as a 2-sided 95% CI and analyzed using Fisher’s exact test and mixed effects modeling with site as a random effect and GA as fixed factor (2-sided *p* < 0.05 considered statistically significant). Analyses of secondary outcomes will be performed according to the intention-to-treat principle using common two-tailed hypothesis tests with alpha equal to 0.05 and using two-sided 95% CIs. Because the analyses of the secondary outcomes are considered exploratory, no correction for type I error will be made. Differences between groups in continuous variables will be analyzed with Student’s *t*-test or, if continuous data is not normally distributed, the Mann–Whitney *U* test will be used. Categorical variables will be compared with the chi-squared test or Fisher’s exact test, as appropriate. Furthermore, mixed effects modeling will be performed with site as a random effect and including randomization stratification factors as appropriate.

The observational part of the study will focus on diagnostic accuracy analysis of presepsin, such as sensitivity, specificity, positive predictive value, negative predictive value, and receiver operating characteristic curves with optimal cut-off values per subgroup.

A detailed statistical analysis plan comprising all study outcomes will be completed before database lock and published separately.

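### At 427 per arm and about six EOS events per arm, the stated pair of 80% power and one-sided 5% error is not attained: either the true error is about 6.5% or the power is about 74%

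*Protocol article*

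**What the plan says.** All inputs come from the Protocol article.

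- **Event rate** (Sample size {14}): "Incidence of culture-proven EOS is assumed to be 1.4"%.
- **Margin** (same section): a "non-inferiority margin of 2% for the absolute between-RCT-arms difference in culture-proven EOS incidence".
- **Size** (same section): "Assuming there is no difference in culture-proven EOS between both study groups, a sample size of 427 is needed in both study groups".
- **Test and error rates** (same section): "using a two-group, large-sample normal approximation test of proportions with 80% power and 1-sided 5% significance level".
- **Allowance for loss** (same section): unassessable cases are "estimated at 5%), a number of 450 will be included in both RCT-arms".
- **Allocation** (Trial design {8}): 1:1.
- **Decision rule** (Statistical methods for primary and secondary outcomes {20a}): "When the upper limit of this one-sided 95% CI is below 2%, non-inferiority can be claimed". The section does not say how the interval is computed. It leaves detail to a statistical analysis plan that will be completed before database lock.

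**The concern.** The sample size rests on a large-sample approximation, while the expected count is 427 × 0.014 = 5.98 events per arm. The chance of three or fewer events in a given arm is 15%. With so few events the estimated Wald standard error is unstable, and it is too small when few events happen to occur. In those samples the upper limit falls below 2% too readily.

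This comparison carries the trial's safety claim on EOS incidence. An anti-conservative rule errs towards accepting the presepsin-guided strategy when the true excess equals the margin. A rule that holds its level gives less chance of showing non-inferiority than the plan states.

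**Working it through.** **1. Reproduce the plan's figure.** With p = 0.014 in both arms, margin 0.02, one-sided 5% (z = 1.645) and 80% power (z = 0.842):

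n = (1.645 + 0.842)² × 2 × 0.014 × 0.986 / 0.02² = 426.7, rounded up to 427.

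427 / 0.95 = 449.5, rounded up to 450. Both stated figures reproduce. Because the assumed rates are equal, pooled and unpooled variances coincide, so the 427 does not show which of the two was used.

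**2. Exact operating characteristics.** Let X₁ ~ Bin(n, p₁) be the count in the intervention arm and X₀ ~ Bin(n, p₀) the count in the control arm, independent. For each rule, sum the joint probability over all pairs (x₁, x₀) for which the upper limit is below 0.02. The error is this sum at p₁ = 0.034, p₀ = 0.014. The power is this sum at p₁ = p₀ = 0.014.

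- Wald limit: p̂₁ − p̂₀ + 1.645 × √[p̂₁(1−p̂₁)/n + p̂₀(1−p̂₀)/n].
- Score limit (Farrington-Manning or Miettinen-Nurminen): the same difference, with the variance taken from the estimates restricted to p₁ − p₀ = 0.02.

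| Rule | n per arm | True error | Power |
|---|---|---|---|
| Wald | 427 | 6.46% | 80.8% |
| Score | 427 | 4.59% | 74.3% |
| Wald | 450 | 6.25% | 82.2% |
| Score | 450 | 4.77% | 76.2% |

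The Newcombe limit has the same operating characteristics as the score limit at both sizes. As an example of where the rules part: with 6 control events and n = 427, Wald allows up to 8 intervention events and the score limit up to 7.

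**3. Is this an artefact of one rate or one rule?** At n = 427, with the true difference at the margin:

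| Control rate | Wald error | Score error |
|---|---|---|
| 0.5% | 7.2% | 4.6% |
| 1.0% | 6.9% | 4.6% |
| 1.4% | 6.5% | 4.6% |
| 2.0% | 5.9% | 4.7% |
| 3.0% | 5.5% | 4.7% |

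Other rules at 427 and 1.4%:

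- Continuity-corrected Wald: error 3.7%, power 71.3%.
- Agresti-Caffo: error 5.5%, power 77.7%.
- Wald statistic with its cut-off tuned to hold 5% at this rate: power 76.0%.
- Score statistic tuned the same way: power 74.5%.

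None of these gives at most 5% error together with 80% power.

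**4. Dependence of power on the rate.** Score-limit power at 427 per arm is 74.3% at 1.4%, 78.9% at 1.2%, 83.8% at 1.0%, 91.1% at 0.7% and 95.3% at 0.5%. The rates below 1.4% are assumptions; the protocol gives none for the moderate-risk group.

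**5. Size for 80%.** At 1.4%, score-limit power is 79.5% at 500 assessable infants per arm and first exceeds 80% at about 502 (80.9%).

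**The case against.** The strongest reply is that the protocol fixes no Wald analysis. The phrase about a normal approximation describes the planning formula, {20a} names no interval, and the choice of interval is commonly left to the analysis plan. This stands. A reader might infer that the trial will run at 6.5% error; the documents do not support that, because it depends on a choice not shown. It does not remove the point. If the analysis plan chooses a score limit, the level is held but the stated 80% power is wrong at the plan's own 1.4%. If it carries the planning test forward, the power is met but the 5% is wrong.

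Three further points also stand.

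- The sample-size arithmetic is right for its formula. It would be wrong to read this as a calculation error.
- The two failures are alternatives. A reader might take 6.5% error and 74% power as occurring together; no single rule does both.
- The shortfall belongs to 1.4%. That rate comes from a cohort of all infants below 32 weeks, while the RCT excludes high-risk infants. If the moderate-risk rate is 1.0% or lower, the score limit exceeds 80% power at 427. The same lower rates raise the Wald error, so the case for naming the score limit becomes stronger.

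The exact shortfall also depends on the method: part of the 74% reflects the score limit's own slight conservatism (4.6%), and the tuned Wald cut-off gives 76%.

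**Conclusion.** The point holds in this limited form. At 1.4% EOS, a 2% margin and 427 per arm, no rule checked delivers both figures stated in Sample size {14}. Either the error is about 6.5% instead of 5%, a relative excess of 6.46 / 5 − 1 = 29%, or the power is about 74% instead of 80%. With all 450 per arm assessable, the alternatives are 6.2% error or 76% power.

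The result assumes independent infants. It ignores the same-arm allocation of multiples described under Sequence generation {16a}. It is a moderate fault that should be corrected before database lock. It does not show that the trial is too small to proceed, since uncertainty about the true moderate-risk rate moves the power by more than this correction does.

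**What to change.** 1. In {20a}, and in the analysis plan, name the Miettinen-Nurminen (score) one-sided 95% upper limit as the rule for the 2% margin, in place of an unspecified interval. Do not use a Wald limit for this decision.
2. In Sample size {14}, restate the power under that rule as about 74% at 427 assessable per arm and 76% at 450, for 1.4% in both arms. Add the values for lower assumed rates: at 427, about 84% at 1.0% and 91% at 0.7%.

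The cost is one sentence and a revised power statement. N stays as it is. The downside is a stated power about 4 points (450 per arm) to 6 points (427 per arm) lower at 1.4%.

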### Recruitment {15}

N/A, as all infants < 32 weeks admitted to the NICU are eligible for inclusion.

## Assignment of interventions: allocation

### Sequence generation {16a}

Randomization will be performed centrally, using web-based block randomization stratified by study site and GA with random permuted blocks within the strata (random block size varying between 4 and 8) with a 1:1 allocation ratio. Randomization sequence is generated using Castor EDC (2019, Castor Electronic Data Capture [online], available at https://castoredc.com), which is regulatory compliant software, ensuring allocation concealment. Multiples (i.e. siblings) will be randomized to the same treatment arm if they both qualify for randomization.

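### Siblings are allocated to the same arm, but neither the sample size nor any named analysis allows for correlation within a pregnancy, so the 80% non-inferiority power is somewhat overstated

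*Protocol article*

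**What the plan says.** Three parts of the protocol article bear on this point.

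- **Allocation.** Sequence generation {16a} keeps multiples together: "Multiples (i.e. siblings) will be randomized to the same treatment arm if they both qualify for randomization". Randomization is stratified by site and gestational age (GA).
- **Sample size.** Sample size {14} takes an EOS incidence of 1.4%, a "non-inferiority margin of 2% for the absolute between-RCT-arms difference in culture-proven EOS incidence", and concludes: "Assuming there is no difference in culture-proven EOS between both study groups, a sample size of 427 is needed in both study groups". The method is given as "using a two-group, large-sample normal approximation test of proportions with 80% power and 1-sided 5% significance level". The superiority outcome is powered with Fisher's exact test. The only inflation is 5% for unassessable cases, giving 450 per arm.
- **Analysis.** Statistical methods {20a} gives the non-inferiority outcome a risk difference with a one-sided 95% interval and names no method for it. The superiority outcome gets Fisher's exact test and "mixed effects modeling with site as a random effect and GA as fixed factor". Secondary outcomes get t, Mann-Whitney, chi-squared or Fisher's tests, and mixed models with site as the random effect plus stratification factors.

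The article mentions no mother or family term, no generalized estimating equations (GEE) and no cluster-robust variance. A separate statistical analysis plan is announced and is not shown.

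**The concern.** Siblings in the same arm share a mother, a site and almost always a gestational age. Maternal risk factors feed the guideline indication for antibiotics. An unblinded team decides whether to stop antibiotics within three days, and this defines the superiority outcome. Some positive correlation within a pregnancy is therefore to be expected, at least for antibiotic exposure.

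Because siblings always fall on the same side of the comparison, positive correlation increases the true variance of the between-arm difference. A standard error that ignores it is too small. For the safety co-primary this works in the unsafe direction: the upper confidence limit is too low, and non-inferiority is easier to claim than the stated one-sided 5% implies. An interval of correct width would have less than the stated 80% power.

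**Working it through.** **Inputs from the article (Sample size):** EOS rate 0.014 in both arms, margin 0.02, one-sided alpha 0.05 (z = 1.645), power 80% (z = 0.842), 5% loss; superiority rates 70% and 40%.

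**Assumptions, because the article gives no figure:** share *f* of randomized infants in same-arm twin pairs, 20-40%; ICC *ρ*, 0.1-0.8.

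**1. Reproduce the stated figure under independence.**
n = (1.645 + 0.842)² × 2 × 0.014 × 0.986 / 0.02² = 426.7, so 427 per arm. Then 427 / 0.95 = 449.5, so 450 per arm. Both match exactly, so no allowance for siblings is contained in either number.

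**2. Design effect.** Each paired infant adds a covariance with one partner, so DE = 1 + *f* × *ρ*. The lowest case is 1 + 0.2 × 0.1 = 1.02 and the highest is 1 + 0.4 × 0.8 = 1.32.

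**3. Power and error rates at 427 per arm.**
SE under independence = √(2 × 0.014 × 0.986 / 427) = 0.00804, and 0.02 / 0.00804 = 2.487.
Non-inferiority power with a correctly sized interval = Φ(2.487/√DE − 1.645).
Actual one-sided size if clustering is ignored = 1 − Φ(1.645/√DE).
Actual two-sided size if clustering is ignored = 2 × [1 − Φ(1.960/√DE)].

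| Share, ICC | DE | Power | One-sided 5% becomes | Two-sided 5% becomes | Evaluable n per arm for 80% |
|---|---|---|---|---|---|
| none | 1.00 | 80.0% | 5.0% | 5.0% | 427 |
| 20%, 0.1 | 1.02 | 79.3% | 5.2% | 5.2% | 436 |
| 30%, 0.3 | 1.09 | 77.0% | 5.8% | 6.1% | 466 |
| 40%, 0.8 | 1.32 | 69.8% | 7.6% | 8.8% | 564 |

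**4. Superiority.** At the largest DE the effective n is 427 / 1.32 = 323 per arm. SE = √((0.7 × 0.3 + 0.4 × 0.6) / 323) = 0.037, and 0.30 / 0.037 is about 8. Power stays above 99.9%.

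**5. Simulation, share 30%.** The non-inferiority check used an unadjusted Wald interval. Its size was taken at true rates of 3.4% and 1.4%, its power at 1.4% in both arms (100,000 runs each). Fisher's size was taken at 70% in both arms (20,000 runs).

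| ICC | Wald non-inferiority size | Wald non-inferiority power | Fisher size |
|---|---|---|---|
| no clustering | 6.5% | 81.1% | 4.4% |
| 0.1 | 6.6% | 80.4% | 4.4% |
| 0.3 | 7.3% | 80.2% | 5.3% |
| 0.8 | 8.6% | 78.9% | 6.8% |

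The Wald size is 6.5% before any clustering, so that part of the excess comes from rare events and not from siblings. Simulated power falls less than in step 3 because the unadjusted interval is kept and its size is allowed to rise. At DE = 1 + 0.3 × 0.8 = 1.24, the formula for that unadjusted interval gives Φ((2.487 − 1.645)/√1.24) = 77.5%, against 72.2% for a correctly sized one.

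**The case against.** The strongest reply is that a mother-level term is ordinary content for a statistical analysis plan, and one is promised. This stands in part: that plan could add the term, and the interval method for the non-inferiority difference is still open. It does not remove the point. The article itself fixes the tests, names site as the only random effect and states the power, and a later analysis plan cannot put a design effect into a power figure already given.

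The second reply is that the effect may be small, and this stands. Under Eligibility criteria (Table 1), an infant whose co-multiple has suspected or proven EOS, or whose mother has suspected or confirmed sepsis, is high risk and not randomized. That plausibly lowers concordance for EOS within randomized pairs, although it acts only on what is known at randomization, within 4 h of birth. Risk class is assigned per infant, so some pairs will split and not both be randomized. In the intervention arm, starting antibiotics depends on each infant's own presepsin result.

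The article does not support four stronger readings that a reader might infer:

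- **That both co-primaries lose power.** Only non-inferiority does.
- **That every named test exceeds its level.** Fisher's test is conservative, and at an ICC of 0.1 its size stays at 4.4%.
- **That the mixed model treats infants as independent.** It accounts for site and GA, two of the sources that siblings share. Only the remaining family level is missing.
- **That the high end of the error range is to be expected.** It needs near-complete concordance within pairs, which the article does not suggest and which Table 1 makes less likely for EOS.

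**Conclusion.** The omission is real and its direction is clear. Siblings are allocated together, the sample size assumes independent infants, and no named analysis has a family-level term. With positive within-pregnancy correlation, standard errors are too small and the stated 80% non-inferiority power is somewhat overstated.

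The size rests on a share of multiples and an ICC that had to be assumed. Over the range used, the loss is from under one to about ten points of non-inferiority power, with about three points in the middle case. If the EOS correlation is near 0.1, the loss is 0.7 to 1.4 points (79.3% to 78.6% at shares of 20-40%). Independence in the non-inferiority interval is inferred from the sample-size method, because the interval method is not stated.

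This is a should-fix point. It does not invalidate the design.

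**What to change.** 1. Record a mother identifier in the trial database.
2. For both co-primary outcomes, report the risk difference with a confidence interval that accounts for clustering by mother. For EOS, about 427 × 0.014 = 6 events per arm are expected, so the method must suit rare events: for example a cluster-adjusted score interval or GEE with a small-sample correction. An uncorrected robust variance or an identity-link model may be unstable with so few events.
3. Keep the unclustered Fisher's test as a supportive check for the superiority outcome.
4. Account for mother-level clustering in the secondary analyses. Most clusters will probably be singletons, so where a mother-level random intercept cannot be estimated, use GEE or robust variance.
5. Restate the non-inferiority power over a declared range for the share of multiples and the ICC. No increase in enrolment is required.

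The cost is a data field, wording in the analysis plan, slightly wider intervals and a slightly lower stated power. Recruitment is expected to run to late 2027 and the analysis plan is due before database lock, so this can be settled before results are known.

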### Concealment mechanism {16b}

N/A, see "Sequence generation {16a}".

### Implementation {16c}

N/A, see "Sequence generation {16a}".

## Assignment of interventions: blinding

### Who will be blinded {17a}

N/A, allocation is not blinded in this study.

### Procedure for unblinding if needed {17b}

N/A, allocation is not blinded in this study.

## Data collection and management

A Trial Master File will be made before the start of the study, with all the essential documents in accordance with Good Clinical Practice guidelines. All data and body-material will be handled confidentially and pseudonymized. A unique subject identification code will be generated for each participant and is not based on the name and day of birth. Body-material will be coded with a barcode before storage in the freezer. The principal investigator of each site will safeguard the key to the unique subject identification code. The key will be stored on a secured drive at the local hospital and is only accessible for the local principal investigator, monitor, auditor, and Health and Youth Care Inspectorate. Study data will be stored in a Castor EDC database, which is regulatory compliant software, handled according to the Personal Data Protection Act. Clinical data will be stored for 15 years and body-material for 5 years. All of the above is registered in a detailed data management plan according to the FAIR principles.

